## Abstract

**Background:**

The impact of mental health problems and disorders in Australia is significant. Mental health problems often start early and disproportionately affect young people. Poor adolescent mental health can predict educational achievement at school and educational and occupational attainment in adulthood. Many young people attend higher education and have been found to experience a range of mental health issues. The university setting therefore presents a unique opportunity to trial interventions to reduce the burden of mental health problems. Mental Health First Aid (MHFA) aims to train participants to recognise symptoms of mental health problems and assist an individual who may be experiencing a mental health crisis. Training nursing students in MHFA may increase mental health literacy and decrease stigma in the student population. This paper presents a protocol for a trial to examine the efficacy of the MHFA training for students studying nursing at a large university in Perth, Western Australia.

**Methods/Design:**

This randomised controlled trial will follow the CONSORT guidelines. Participants will be randomly allocated to the intervention group (receiving a MHFA training course comprising two face to face 6.5 hour sessions run over two days during the intervention period) or a waitlisted control group (not receiving MHFA training during the study). The source population will be undergraduate nursing students at a large university located in Perth, Western Australia. Efficacy of the MHFA training will be assessed by following the intention-to-treat principle and repeated measures analysis.

**Discussion:**

Given the known burden of mental health disorders among student populations, it is important universities consider effective strategies to address mental health issues. Providing MHFA training to students offers the advantage of increasing mental health literacy, among the student population. Further, students trained in MHFA are likely to utilise these skills in the broader community, when they graduate to the workforce. It is anticipated that this trial will demonstrate the scalability of MHFA in the university environment for pre-service nurses and that implementation of MHFA courses, with comprehensive evaluation, could yield positive improvements in the mental health literacy amongst this target group as well as other tertiary student groups.

**Trial registration:**

Australian New Zealand Clinical Trials Registry ACTRN12614000861651.

## Background

### Mental health and young people in Australia

The impact of mental health problems and disorders in Australia is significant. In the most recent national Australian mental health survey, almost half of respondents had experienced a mental health disorder at some point in their lives, and around one in five respondents aged 16–85 had experienced a mental health disorder in the preceding 12 months [1]. The most common mental health disorders are depressive, anxiety and substance use disorders, which are often comorbid [1].

Mental health disorders often start early with the first presentation for most mental health problems occurring between the ages of 18 and 29 [2]. Mental health problems also disproportionately affect young people [2] with 16–24 years olds experiencing the highest prevalence of mental health disorders than any other age group [3]. National data suggests that around 1 in 4 people aged 16–34 years had experienced a mental health disorder in the last 12 months [1] and that mental health disorders for those aged 15–44 years contributed to over a third (36%) of Australia’s Disability-Adjusted Life Years [4]. Common mental health disorders in young Australians aged 16–24 years are: anxiety disorders (15.4%), depressive disorders (6.3%) and substance use disorders (12.7%) [3].

### Mental health and university students

Poor adolescent mental health has been found to predict educational achievement at school and educational and occupational attainment in adulthood [5-9].This is of concern for the tertiary environment as over a quarter of young Australian adults aged 18 to 35 attend higher education [10] and increased levels of psychological distress may impair students’ academic capabilities in the university setting [11]. For example, a survey of US and Canadian college students (n = 71,860), found seven of the top ten health-related barriers to successful academic performance were related to mental health. In particular, stress was identified as the biggest barrier, affecting around a third of the students (33.9%); a diagnosis of either depression, anxiety disorder, or seasonal affective disorder was the 6th barrier (affecting 16.1% of students); and alcohol misuse was the tenth barrier (affecting 7.8% of students) [12]. Some studies indicate that mental health problems may be higher among university students compared to their non-tertiary student peers [13-18]. For example, a survey of two Australian universities found that most students (83.9%) reported higher levels of psychological distress when compared to the general population (29%) [11]. Further, students may not seek help for their mental health problems [14,19]. Reasons for this may include suicidal thoughts, perceived need for self-reliance, perceived stigma of talking to professionals, believing that nothing will assist, unfamiliarity or awareness of services or perception that stress is a normal part of study [20-22]. Financial strain and lower socio-economic status, or being a young or a female student may lead to higher levels of psychological distress, increasing the risk for poorer mental health [11,13,15,19,23-27]. This is significant as the Australian government aims for more, young, and socioeconomically disadvantaged people to complete a university qualification [28].

### Mental health literacy

Jorm et al. [29], suggested mental health literacy incorporates several components: “(a) the ability to recognise specific disorders or different types of psychological distress; (b) knowledge and beliefs about risk factors and causes; (c) knowledge and beliefs about self-help interventions; (d) knowledge and beliefs about professional help available; (e) attitudes which facilitate recognition and appropriate help-seeking; and (f) knowledge of how to seek mental health information” [29]. The most recent Australian survey of mental health literacy, undertaken in 2011, was compared to surveys taken in 1995 and 2003–4 [30]. It found mental health literacy among the general population had improved in every aspect excluding ‘stigmatising attitudes’ [30]. However, aspects such as ‘recognition of mental disorders’, ‘beliefs about prevention’ and ‘stigmatising attitudes’ were not significantly improved in young people [30]. Research has shown that improving the mental health literacy of a community not only decreases the stigma of mental health but also improves the mental health of community members [31]. Additionally, simple recognition of the name and a few characteristics of a mental health condition can decrease stigma towards those living with mental health problems and disorders [31]. Recognising a mental health disorder and lowering stigma also leads to more help seeking from relevant sources [32].

### Mental health literacy in the university setting

Whilst a number of interventions have been trialed to address mental health issues in universities [33-40], a greater focus on increasing mental health literacy may be valuable where mental health problems and stigmatising attitudes are common [41,42], and health literacy and help-seeking behaviours may be poor [41,43]. For example, a recent study implemented in an Australian university found that talking to a close friend or family member (as opposed to a health professional) was one of the most common forms of help seeking [42]. Another study found pharmacy students who participated in MHFA courses were better able to correctly identify mental illnesses and their treatments, held less stigmatising views toward mental illness, and reported greater confidence in delivering pharmacy services to those with a mental health problem [44].

### Training pre-service nurses

In Western Australia, there is a mental health workforce shortage across a range of disciplines [45]. Nurses constitute over half of Australian mental health healthcare providers and therefore play an important role in delivering quality early intervention and treatment for mental health disorders and problems [45].The attitudes of nurses towards mental health problems and those experiencing them are important as they have the potential to be stigmatising and discriminatory or very supportive [46]. Some sources have suggested that Australian nurses have low or even inadequate levels of mental health nursing skills when they enter the workforce [47,48]. Targeting students studying nursing may increase health literacy and decrease stigma in the student population at an early stage. It may also influence their attitudes towards mental health after graduation, encouraging best practice, client-centered care. A longitudinal study by McCann et al. found when nursing students begin their studies, they have a mental health literacy level analogous to that of the general public [47]. Further research by Ward suggested that structured training programs examining mental health issues increased nursing students’ confidence and preparedness to respond to mental health issues, and students indicated a desire for greater levels of education and training support [49].

### Mental health first aid

Mental health promotion, prevention and early intervention strategies have been shown to demonstrate positive outcomes [50] and have been a focus of Australian government policy for the past decade [51]. Given the high prevalence and burden of mental health disorders among student populations, trialing a range of interventions (universal, selective, indicated prevention and early intervention) [52] within the university setting to reduce negative mental health outcomes is important [39]. Mental Health First Aid courses were developed by Mental Health First Aid Australia (MHFA) in 2000 [53,54]. These courses primarily aim to train participants to recognise symptoms of mental health problems and assist someone who may be experiencing a mental health crisis. The course includes scenarios focusing on common mental health issues such as panic attacks, suicidal ideation, in addition to focusing on risk factors, signs and symptoms for mental health problems and disorders such as depression and anxiety [53,54]. In 2011, just ten years after commencement, 170,000 Australian adults had received MHFA training and over 850 instructors had been trained [55]. The MHFA program has been selected as one of 10 global initiatives to demonstrate “radical efficiency” due to its ability to deliver greater public outcomes than previous interventions at a reduced cost [56]. These courses have reportedly demonstrated increased mental health literacy and mental health of course participants and decreased stigma around mental health problems and disorders [57]. It is recognised that one of the challenges highlighted in the literature is that there are few studies that demonstrate the longer term impact of Mental Health First Aid on helping behaviours or participants’ subsequent experiences in providing first aid. However, those that have been conducted point to a positive outcome from Mental Health First Aid delivery in real-life practice though it has been suggested that this may require further exploration [58-61].

The Australian Government Department of Health has provided funding to Mental Health First Aid Australia [62] to specifically train frontline staff including financial counsellors and healthcare professionals (including pre-service nursing students) to better identify and respond to the needs of people at risk of mental health problems and disorders. The aim of the course developed for nursing students is to teach them how to assist a peer who is developing a mental health problem or in a mental health crisis. The course is available both as a face to face version and as an e-course online [63].

This paper presents a protocol for a pragmatic, low-cost trial to examine the efficacy of the MHFA training for students studying nursing at a large university in Perth, Western Australia. The primary outcome is changes in mental health literacy, which will be measured in terms of confidence in dealing with mental health problems, recognition of and knowledge about mental health problems, first aid intentions, stigmatising attitudes and social distance.

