### Instruments

A self-report questionnaire will measure confidence to respond to mental health problems, recognition of and knowledge about mental health problems, first aid intentions towards someone experiencing a mental health problem, stigmatising attitudes [67] and social distance [68-70]. The questionnaire is based on those used in national surveys of adults [43] and young people [71] and further developed for use with the MHFA course [54,65,69], and described in detail in previous studies [44,57,72]. Questions related to confidence, recognition, intentions, stigmatising attitudes and social distance will be introduced with a vignette describing a young person with symptoms of a mental health problem. The use of the vignette to introduce mental health issues has been used successfully by other studies, including those of MHFA [44,57,68,72]. Participants will be asked about their level of confidence to help and what they would do to assist the person in the vignette [65]. Knowledge will be measured using 16 questions developed by MHFA and modified for use with young people [66]. Stigmatising attitudes will be measured using personal and perceived stigma scales [67], and social distance will be measured using a five item social distance scale [68]. The scales have been used widely and previously tested for reliability and validity; the stigma scales have demonstrated test-retest reliability and acceptable internal consistency while the social distance scale has been shown to be a reliable measure of stigma towards people with mental health problems and to be valid as a proxy measure for rejection of and discrimination toward people with mental health problems and disorders [67,69,70,73]. The questionnaire will be administered to the intervention and control group participants at three time intervals: baseline, immediately post, and two months after the intervention. Basic socio-demographic characteristics of participants will be collected at baseline only.

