### Statistical analyses

The intention-to-treat principle will be followed, where all participants who completed the baseline questionnaire will be included in the analysis regardless whether they complete the whole intervention. Acknowledging there may be attrition at the follow-up, the missing values for the non-respondents will be recorded using their baseline scores. If the missing data are at random, the imputation method will be applied [59]. This will assure no false improvement in efficacy. Data will be analysed using SPSS Version 22.

The demographics of the participants in the intervention and control groups will be compared using the independent samples t-test or Pearson’s Chi-square test to measure differences including age, gender and country of birth. The primary outcome measures (described above) will be calculated following validated MHFA scoring methods reported in the literature [44,54,57,65-68]. Repeated measures analysis of variance will be employed to assess continuous measures between the intervention and control group over three time points (baseline, post intervention and two months post intervention). Logistic regression will be used to assess changes in dichotomous variables. The significance level will be set at 5%.

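### Six to seven co-equal primary measures share an unadjusted 5% level, with no lead measure, primary time point or rule for claiming efficacy

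*Protocol article*

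**What the plan says.** All references are to the protocol article.

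- **Background, Mental health first aid.** The primary outcome is given as a single construct: "The primary outcome is changes in mental health literacy, which will be measured in terms of confidence in dealing with mental health problems", and then "recognition of and knowledge about mental health problems, first aid intentions, stigmatising attitudes and social distance". That is six domains. No total literacy score is defined.
- **Instruments.** "Stigmatising attitudes will be measured using personal and perceived stigma scales". Counting these two scales separately gives seven measures. The questionnaire is given at "baseline, immediately post, and two months after the intervention". Neither post-baseline assessment is marked as the primary one.
- **Statistical analyses.** The measures are primary in the plural: "The primary outcome measures (described above) will be calculated following validated MHFA scoring methods reported in the literature". For the continuous ones, "Repeated measures analysis of variance will be employed to assess continuous measures between the intervention and control group over three time points". For the others, "Logistic regression will be used to assess changes in dichotomous variables". The error rate is fixed in one sentence: "The significance level will be set at 5"%.
- **Participants and sample size.** The calculation (50 per group, 5% level, 90% power, baseline–post correlation 0.8, recruitment of 63 per group for 20% attrition) refers to medium effects in the outcome variables generally. It does not single out a measure either.

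**The concern.** The trial sets out to determine whether the training is efficacious, and its primary outcome is where that question is answered. With several measures all called primary, each judged at 5%, and nothing said about how many must succeed, the decision is left open until the results are known. A trial with one significant scale out of seven could be reported as having improved mental health literacy. So could a trial with all seven significant, although the evidence would be very different.

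Two things are at stake. The false-positive risk attached to the main claim is not controlled at the stated 5%. And the scale, or the time point, on which the claim rests could be chosen after the data are seen.

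**Working it through.** **1. The plan's own figures.** Attrition: 50/(1 − 0.20) = 62.5, rounded up to 63, which agrees with the article. The 50 cannot be checked uniquely because no number is given for a medium effect. Taking d = 0.5 as an assumption, r = 0.8, two-sided 5% and 90% power:

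- baseline-adjusted analysis: n = 2(1.960 + 1.282)² × (1 − 0.8²)/0.5² = 2 × 10.51 × 0.36/0.25 = 30.3, so 31 per group;
- change score: n = 2 × 10.51 × 2(1 − 0.8)/0.25 = 33.6, so 34 per group.

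Working backwards, 50 per group at 90% power corresponds to d of about 0.39 (baseline-adjusted) to 0.41 (change score).

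**2. Number of tests.** Six measures by the list in the Background; seven once stigma is split as in Instruments. The planned repeated measures analysis takes in all three time points in one model, so I count one treatment test per measure. The article does not say how many tests each dichotomous measure will have; I take one there too.

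**3. Chance of at least one false positive**, all null hypotheses true, each test two-sided at 5% (sidedness is not stated; two-sided is assumed). For independent tests it is 1 − 0.95^k:

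- k = 6: 1 − 0.7351 = 26.5%
- k = 7: 1 − 0.6983 = 30.2%

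For equally correlated normal test statistics (simulation, 400,000 draws):

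| Assumed correlation between measures | 6 measures | 7 measures |
|---|---|---|
| 0 | 26.5% | 30.2% |
| 0.3 | 24.1% | 27.1% |
| 0.5 | 20.8% | 22.9% |
| 0.8 | 13.9% | 14.8% |

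The article's 0.8 is a baseline–post correlation within a measure. It says nothing about the correlation between measures, so the rows above are a range of assumptions.

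**4. What adjustment across seven measures would cost.** The strictest Holm step is 0.05/7 = 0.00714. Power is for one measure, from the noncentral t distribution with 50 per group.

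- *From the plan's own statement.* If 50 per group gives 90% at two-sided 5%, the noncentrality is about 3.27. Power at 0.05/7 is then about 70%.
- *From an assumed d = 0.5 with r = 0.8.* Baseline-adjusted: noncentrality 0.5/(0.6 × √(2/50)) = 4.17, power 92%. Change score: noncentrality 0.5/(0.632 × √(2/50)) = 3.95, power 88%.

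These figures are for continuous measures only and do not carry over to those analysed by logistic regression.

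**The case against.** Several objections have force.

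- **The success rule is not written.** A family-wise error rate describes a trial that claims success on any one measure. If every measure had to improve, the error rate would be below 5%. This stands: the defect is that the rule is unspecified, and the 15–30% is conditional on one reading of it. Nothing in the text excludes that reading.
- **Multiplicity methods are often left to the analysis plan.** This is true, and the absence of a named adjustment would not by itself be a finding. But which outcome is primary is a protocol matter, and the article settles it: all the measures are primary, at a flat 5%.
- **The count is a reading.** Six is as defensible as seven, and the table shows both. The conclusion does not turn on it.

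Two stronger readings are tempting. The documents support neither.

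- A reader might count seven measures at two follow-ups as fourteen separate 5% tests, which gives about 37–48% under moderate assumed correlations. The article does not plan those tests: for continuous measures it specifies one repeated measures analysis over three time points. Separate tests at each follow-up would raise the risk above the 15–30% range, but that is a conditional remark and not the plan.
- A reader might also infer that adjusting across all seven costs almost nothing, from the 88–92% power at d = 0.5. That effect size is not in the article, and baseline adjustment is not the stated analysis. On the article's own combination of 50 per group and 90% power, the cost is a fall to about 70%.

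**Conclusion.** The point holds in this form: the article designates six to seven co-equal primary measures at an unadjusted 5%, without a lead measure, a primary time point or a rule for claiming efficacy. The main claim therefore has no controlled error rate. If one significant measure were enough, the chance of a false primary claim would be about 15–30% for seven measures (14–27% for six), three to six times the stated 5%. This assumes one two-sided test per measure, all nulls true, and between-measure correlations of 0.8 to 0. The designation and the flat 5% are read directly from the text; the size depends on those assumptions.

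**What to change.** Before any outcome data are analysed, name one primary measure at one time point, for example the 16-item knowledge score at two months, tested at two-sided 5%. Make the other scales and the other time point secondary, and state that efficacy will be claimed only on the primary comparison. This is a change of wording: it needs no more participants and leaves the planned 5% level intact. The cost is that the remaining scales lose primary status, so a benefit seen only on, say, stigma would be reported as supportive.

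If all measures are to stay primary, name one time point, apply Holm across them, and restate the power with the assumed effect size written down. On the article's figures that option drops power at the strictest step from 90% to about 70%; at an assumed d = 0.5 with r = 0.8 it is about 88–92%. Whether 50 per group is still enough would then have to be decided openly.
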